#### Secondary outcomes

Surgeons determined which of their respective patients may be candidates to participate in secondary outcomes data collection. Surgeons introduced this part of the study to appropriate patients and if the individual was agreeable, the study team approached the respective patient to obtain written informed consent. Patients were not approached if they were too ill, frail or psychologically vulnerable, as determined by the participating surgeon. Patients required sufficient command of the English language and capacity to give informed consent. Secondary outcomes included:

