### Intervention

The QIRC strategy is a set of interventions directed at surgeons working in a given hospital. The interventions include: a workshop, use of opinion leaders, operative demonstrations, a post-operative questionnaire, as well as audit and feedback.

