### Outcome measures

#### Primary outcomes

Since the hospital is our unit of analysis it is imperative that consecutive patients be included to prevent surgeon selection bias (e.g., excluding patients with difficult tumours perceived as high-risk for negative outcomes). Three methods of patient accrual were used to ensure consecutive patient accrual for primary outcomes – regular (weekly) phone calls to surgeons' offices, review of operating room booking logs, and hospital health records queries. Patient consent was not obtained for primary outcomes since data were collected via retrospective chart review and involved no patient contact. Primary outcomes included:

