### Analysis

We will use the intention-to-treat principle to analyse data. We will use multiple imputation to handle missing data [42]. Treatment arms will be compared with respect to potential covariates using continuous and categorical univariable analyses. This will include patient (age, sex, comorbidities, weight and height), treatment (adjuvant therapies), tumour (stage, node counts, margin status, other histology measures), and hospital (teaching status, procedure volume) level variables. Methods of analysis, including adjustment for covariates, will use the cluster randomization trial design [38,39]. Specifically, the primary outcomes of colostomy rate and local recurrence rate will be assessed using a nested (cluster) analysis model that will consider the correlation of outcomes within each hospital, and the influence of covariables. Adjustments for adjuvant therapies are especially important since it is likely these treatments will not be delivered among centers using a standard regimen. The major design factor will be arm of study (experimental or control). No adjustment will be made for multiple comparisons of primary outcomes since each is of interest on its own. Secondary analyses will be conducted on bowel, bladder and sexual function, and quality of life using nested analysis of variance. We will conduct analyses using the latest versions of SAS, SPlus and StatXact software as needed. The trial will be reported according to the CONSORT standards for reporting cluster-randomized trials [43]. The results will be expressed as odds ratio [OR] (for binary outcomes), hazard ratio [HR] (for time-to-event outcomes) or mean difference (for continuous outcomes), with corresponding standard errors, 95% confidence intervals and associated p-values. P-values will be reported to three decimal places with p-values less than 0.001 reported as p < 0.001. For all tests, we will use alpha = 0.05 level of significance. We will examine residuals to assess goodness-of-fit and model assumptions for all analyses as appropriate.

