## Discussion

The QIRC trial will assess if the QIRC strategy, which is designed to positively influence surgeon practice at a given hospital, can lead to improved patient outcomes of rectal cancer surgery. Lower permanent colostomy and local tumour recurrence rates in the intervention arm would suggest that the QIRC strategy is efficacious. The strategy may also act as a template for efforts to improve surgical quality in other cancer sites.

Participants in a clinical trial may alter – improve – their behaviour in response to being observed rather than as a result of a study intervention [49,50]. This phenomenon is known as the Hawthorne effect and it is important to consider in trials designed to influence physician behaviour and action. Surgeons in both arms of the QIRC trial may be subject to a potential Hawthorne effect. Surgeons in the control arm will consent to randomization and be cognizant of ongoing data abstraction. In addition to these maneuvers, surgeons in the experimental arm will receive the QIRC strategy. Thus, all surgeons in the study will be aware their actions are being observed. Any improvement in patient outcomes in the experimental arm must be above and beyond the Hawthorne effect, and would be attributed to the intervention.

We are aware of one other trial that tested if knowledge translation or quality improvement methods could influence (i.e., improve) surgeon practice [51]. This trial used continuing medical education and opinion leaders to improve (i.e., lower) rates of cesarean section. The relatively small number of randomized trials that involve surgeons usually compare the delivery of contrasting treatments (e.g., surgical versus medical therapy for patients with carotid stenosis, or, different methods of surgically treating patients with breast cancer). Thus, regardless of our results, successful engagement of surgeon participation in this cluster-randomized trial will be an important observation in and of itself. This trial does not compare total mesorectal excision-type surgery versus standard surgery, rather it is comparing a strategy designed to influence surgeon practice versus the normal environment. Thus, the trial will contribute greatly to knowledge on optimizing surgeon practice.

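### The secondary quality-of-life and function comparison is exposed to selection that could differ by arm, because surgeons who know their allocation decide which patients may be approached

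*Protocol article*

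**What the plan says.** The Protocol article treats its two outcome families differently.

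- **Primary outcomes.** The section of that name holds that "it is imperative that consecutive patients be included to prevent surgeon selection bias". It adds that "Three methods of patient accrual were used to ensure consecutive patient accrual for primary outcomes". No patient consent was sought, because the data come from charts.
- **Secondary outcomes.** Here "Surgeons determined which of their respective patients may be candidates to participate in secondary outcomes data collection". The section continues: "Surgeons introduced this part of the study to appropriate patients and if the individual was agreeable, the study team approached the respective patient" for written consent. It also states: "Patients were not approached if they were too ill, frail or psychologically vulnerable, as determined by the participating surgeon". Adequate English and capacity to consent were required as well.
- **Who the surgeons are.** Under Intervention, "The QIRC strategy is a set of interventions directed at surgeons working in a given hospital". Under Discussion, "Surgeons in the control arm will consent to randomization and be cognizant of ongoing data abstraction".
- **Timing.** Under Randomization, patient accrual starts once a site has been randomised. Under Data gathering, the baseline questionnaire may be taken before the operation or up to four weeks from it.
- **Analysis.** The Analysis section says: "Secondary analyses will be conducted on bowel, bladder and sexual function, and quality of life using nested analysis of variance". It also refers in general terms to intention to treat, multiple imputation and covariate adjustment.

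**The concern.** The plan names surgeon selection as a threat and guards against it for colostomy and local recurrence. For the patient-reported outcomes, the same surgeons act as first gatekeeper. The grounds they apply are matters of judgement and are plausibly related to the scores being measured.

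In a cluster trial, randomising hospitals balances the hospitals. It does not balance a patient subset picked afterwards by people who know the arm. Intervention surgeons have a workshop, a local opinion leader, visiting experts and feedback on their results. Control surgeons have none of these. The two groups could therefore apply different thresholds for putting a patient forward.

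At stake is the stated secondary hypothesis that scores are higher in intervention hospitals. A difference could partly reflect who was approached, and a true difference could be masked in the same way.

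**Working it through.** The plan gives no sample size, expected participation or effect size for the secondary outcomes, so there is no figure to reproduce. The check is a reading of the sections together, followed by an illustration with assumed inputs.

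**Reading the sections together**

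1. *Does the gatekeeper know the arm?* The document does not use the word unblinded. It follows from the design: surgeons consent to randomisation, and only one arm receives the surgeon-directed activities.
2. *Does selection come after allocation?* Yes, because accrual follows site randomisation.
3. *Can it come after the operation?* Yes, because the baseline window extends to four weeks from surgery. The surgeon may then already know the early course.
4. *Is the criterion related to outcome?* Illness, frailty and psychological vulnerability plausibly are.
5. *Does another stated safeguard cover it?* The three accrual checks are stated for primary outcomes. Trained telephone assessors protect measurement, not entry to the sample. Nested analysis of variance handles clustering, not selection. Multiple imputation could reach patients never approached only if they were kept in the analysis set, which the document does not say.

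**Illustration (all inputs assumed, no true effect)**

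Let 30% of patients be frail, and let 80% of non-frail patients be included in both arms. Let frail patients score lower by D standard deviations (SD).

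- Frail share of the subset = 0.3q / (0.3q + 0.7 × 0.8), where q is the proportion of frail patients included.
- Spurious difference = (control frail share − intervention frail share) × D.

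| q, intervention | q, control | Frail share, intervention | Frail share, control | D = 0.5 | D = 1.0 |
|---|---|---|---|---|---|
| 0.6 | 0.6 | 0.243 | 0.243 | 0 | 0 |
| 0.4 | 0.6 | 0.176 | 0.243 | 0.033 SD | 0.067 SD |
| 0.2 | 0.6 | 0.097 | 0.243 | 0.073 SD | 0.146 SD |

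The first row is the important one: equal selection gives no bias between arms. Swapping the two arms' q values reverses the sign.

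A second model gives the same order of size. Suppose surgeons withhold the worst 10% in one arm and the worst 20% in the other, on a normally distributed trait. The mean of those kept is φ(z)/(1 − p):

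- p = 0.20: 0.2800/0.80 = 0.350
- p = 0.10: 0.1755/0.90 = 0.195
- Difference: 0.155 SD if the trait is the score itself, or 0.155 × 0.5 ≈ 0.08 SD if it correlates 0.5 with the score

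**Scale**

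If all 336 planned patients per arm took part and there were no clustering (both optimistic), the 95% half-width for a mean difference would be 1.96 × √(2/336) ≈ 0.15 SD. Most of the illustrated values lie below that.

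**The case against.** The strongest defence is that the two sections do not contradict each other. Consecutive inclusion is possible for chart review without consent. Questionnaires need contact and written consent, so a complete sample cannot be guaranteed, and introduction by the treating surgeon protects vulnerable patients from unsolicited contact. That stands: surgeon introduction is a defensible recruitment route. It explains an incomplete subset, but it does not make the arms comparable within it.

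Three stronger readings are tempting, and the text supports none of them.

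- *That the comparison is biased.* Nothing shows that thresholds differed by arm.
- *That surgeons alone chose who gave data.* Patients had to agree and then consent, which is a second filter.
- *That patients with stomas or poor function were screened out.* Neither is a listed ground, and the only feedback content given as an example is the colostomy rate, not quality of life.

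It is also fair to say that the article condenses a fuller protocol. Participation logs or detailed handling of the subset may exist there, and their absence here is not the point. The point is the recruitment rule that the article does state; later analysis can mitigate it but cannot undo it. Baseline scores would help if adjusted for, but they may be post-operative and do not exist for patients never approached.

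**Conclusion.** The concern holds as one of exposure. Surgeons who know their arm, and whose behaviour the trial sets out to change, screen patients after randomisation on subjective grounds related to prognosis. The analysis named for these outcomes has no stated step for that.

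Whether bias results depends on selection differing by arm, which the document neither shows nor excludes. Size and direction therefore cannot be fixed. The values from 0 to about 0.15 SD rest wholly on assumed inputs and illustrate the mechanism only. If selection was equal, the loss is confined to generalisability.

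A reader might infer that the trial's main result is compromised. It is not: both primary outcomes rest on consecutive chart review.

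**What to change.** The Surgeon survey section describes accrual as completed, so recruitment cannot be redesigned. The analysis is still to come, and three steps are open.

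1. **Describe the selection.** Use the chart data gathered on all consecutive patients to compare participants with non-participants, by arm and by hospital. Compare age, sex, comorbidity and other pre-operative variables, and report participation on the same breakdown.
2. **Add a supporting analysis.** Alongside the nested analysis of variance, fit a model that respects clustering and is either weighted by the inverse probability of participation or adjusted for those variables. Model participation by arm, so that different thresholds can show.
3. **Limit the conclusion.** State that the secondary result applies to a surgeon-selected, consenting subset, not to the randomised cohort.

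The cost is mainly analysis time, since the data are collected anyway for the primary outcomes. Intervals will widen by an amount the documents do not allow one to state, with only eight hospitals per arm. Weighting or adjustment gives no protection against unmeasured selection on frailty or psychological vulnerability, and cannot represent types of patient who were never approached. Step 3 is therefore needed whatever step 2 shows.

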#### Quality of life

To assess overall impact of disease and treatment on patient quality of life we used the following: the European Organization for Research and Treatment of Cancer (EORTC) QLQ-C30 [35], an instrument to assess quality of life in cancer patients; the supplemental EORTC QLQ-CR38 [36], a colorectal cancer-specific quality of life questionnaire module; and, the 36-Item Short Form Health Survey, Version 2 (SF-36) [37].

#### Bowel, bladder and sexual function

At the time of trial initiation we felt there was no validated instrument(s) that adequately addressed these three important domains. To this end a brief set of questions were developed [see Additional file 2].

### Sample size

We calculated the intracluster correlation coefficient using the a priori variation in permanent colostomy rates among hospitals in Ontario with a rectal cancer procedure volume of at least 15 per year for years 1997 to 1999 (Intracluster correlation = 0.4) [38,39]. We used a conservative spectrum of values for local recurrence intraclass correlation coefficients. Alpha and beta were set at 0.05 and 0.2, respectively. Tests were two-sided and assumed that a clinically important change would consist of decrease in the baseline rate of permanent colostomy from 30% to 15%. Using permanent colostomy as the outcome, the study required 8 hospitals and 311 patients in each arm. For local recurrence we extrapolated from the literature, and assumed that local recurrence rates are a conservative 20% and can be brought down to 8% in the intervention arm. To detect this difference with confidence we required 16 hospitals and 672 patients – 8 hospitals and 336 patients in each arm. Thus, the sample size required for the outcome local recurrence determined our final sample size requirements. We randomized 16 hospitals and anticipated an accrual period of 24 months.

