**Methods and Design:**

Hospitals were randomized to the QIRC strategy (experimental group) versus normal practice environment (control group). Participating hospitals, and the respective surgeon group operating in them, are from Ontario, Canada and have an annual procedure volume for major rectal cancer resections of 15 or greater. Patients were eligible if they underwent major rectal surgery for a diagnosis of primary rectal cancer. The surgeon-directed QIRC interventions included a workshop, use of opinion leaders, operative demonstrations, a post-operative questionnaire, and, audit and feedback. For an operative demonstration participating surgeons invited a study team surgeon to assist them with a case of rectal cancer surgery. The intent was to demonstrate total mesorectal excision techniques. Control arm surgeons received no intervention. Sample size calculations were two-sided, considered the clustering of data at the hospital level, and were driven by requirements for the outcome local recurrence. To detect an improvement in local recurrence from 20% to 8% with confidence we required 16 hospitals and 672 patients – 8 hospitals and 336 patients in each arm. Outcomes data are collected via chart review for at least 30 months after surgery. Analyses will use an intention-to-treat principle and will consider the clustering of data. Data collection will be complete by the end of 2007.

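### The printed intracluster correlation of 0.4 for permanent colostomy cannot give 8 hospitals and 311 patients per arm; the stated sizes imply a value about one tenth as large

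*Protocol article*

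**What the plan says.** All the inputs stand in one paragraph of the protocol article, under Sample size.

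- **ICC, colostomy.** It was estimated from the variation in colostomy rates among Ontario hospitals with a volume of "at least 15 per year for years 1997 to 1999 (Intracluster correlation = 0.4").
- **ICC, local recurrence.** No number is given: "We used a conservative spectrum of values for local recurrence intraclass correlation coefficients".
- **Error rates.** "Alpha and beta were set at 0.05 and 0.2, respectively", with two-sided tests.
- **Colostomy.** The target is a fall from 30% to 15%, and "Using permanent colostomy as the outcome, the study required 8 hospitals and 311 patients in each arm".
- **Local recurrence.** The target is a fall from 20% to 8%: "To detect this difference with confidence we required 16 hospitals and 672 patients", that is 8 hospitals and 336 patients per arm. The abstract repeats this size. Both places say that recurrence determined the final size.

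**The concern.** In a cluster trial the ICC and the cluster size together set how far the sample must be inflated beyond that of an individually randomised trial. Hospitals of about 40 patients with an ICC of 0.4 would need a design effect above 16, yet 311 is less than three times the individually randomised size. Either the printed ICC or the colostomy size and power that go with it must be wrong.

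Two kinds of reader are affected. Someone judging how informative a null colostomy result would be cannot tell whether the design had 80% power or about 20%. Someone planning another surgical cluster trial may take 0.4 as an empirical estimate for Ontario hospitals and be out by a factor of about ten.

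**Working it through.** **Inputs.** From Sample size: two-sided alpha 0.05, power 80%, 30% versus 15%, 20% versus 8%, 8 hospitals per arm, 311 and 336 patients per arm, ICC 0.4 for colostomy. Cluster sizes are not stated. Dividing gives 311/8 = 38.875 and 336/8 = 42 patients per hospital.

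**Step 1: size without clustering.** n = (1.96 + 0.8416)² × [p1(1−p1) + p2(1−p2)] / (p1−p2)², where (1.96 + 0.8416)² = 7.849.

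- Colostomy: 7.849 × 0.3375 / 0.0225 = 117.73 per arm.
- Recurrence: 7.849 × 0.2336 / 0.0144 = 127.33 per arm.

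**Step 2: try to reproduce 311 with ICC 0.4.** Design effect DE = 1 + (m − 1) × ICC = 1 + 37.875 × 0.4 = 16.15. Required n = 117.73 × 16.15 = about 1,901 per arm, or 1,901/38.875 = about 49 hospitals per arm. The stated size is not reproduced.

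**Step 3: can more patients per hospital help?** As m grows without limit, the effective size per arm tends to (number of hospitals)/ICC = 8/0.4 = 20. Against 117.73 needed, no enrolment is enough with 8 hospitals. The minimum is 117.73 × 0.4 = 47.1, so at least 48 hospitals per arm.

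**Step 4: power at the stated size with ICC 0.4.** Effective n = 311/16.15 = 19.3 per arm. The standard error is √(0.3375/19.3) = 0.132, so z = 0.15/0.132 − 1.96 = about −0.83 and power is about 20%. Pooled variance gives 19.5%, and a t version with 14 degrees of freedom gives 18%. At the ceiling of 20 effective patients, power is 21%.

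**Step 5: which ICC do the stated sizes imply?** ICC = (N/n − 1)/(m − 1), using each size's own m.

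- Colostomy: (311/117.73 − 1)/37.875 = 1.642/37.875 = 0.043.
- Recurrence: (336/127.33 − 1)/41 = 1.639/41 = 0.040.

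| Formula | Colostomy | Recurrence |
|---|---|---|
| Unpooled variance | 0.043 | 0.040 |
| Pooled variance | 0.042 | 0.039 |
| Continuity correction | 0.035–0.036 | 0.032–0.033 |

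A t-based calculation implies about 0.031–0.034.

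**Step 6: one parameter set for both sizes.** Take ICC 0.04 and m = 42 throughout: DE = 1 + 41 × 0.04 = 2.64.

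- Colostomy: 117.73 × 2.64 = 310.8 (stated 311). 310.8/42 = 7.4 hospitals, which rounds up to the stated 8.
- Recurrence: 127.33 × 2.64 = 336.1 (stated 336). 336.1/42 = 8.0 hospitals.

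**The case against.** The best attempt to save 0.4 is to suppose another formula or another meaning. A one-sided test does not help: (1.645 + 0.8416)² × 15 = about 93 effective patients per arm would still be needed, against a ceiling of 20. Reading 0.4 as a between-hospital coefficient of variation comes closer. With hospitals per arm = 1 + 7.849 × [0.3375/38.875 + 0.4² × (0.30² + 0.15²)]/0.0225, colostomy needs 10.3 hospitals per arm, not 8. The same formula gives 8.1 for recurrence, but the article attaches 0.4 to colostomy and calls it a correlation.

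Other objections limit how far the point goes, and they stand.

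- **The whole design.** A reader might infer that the trial as printed has about 20% power for both primary outcomes. The article assigns 0.4 to colostomy alone. For recurrence it mentions only a range of values, and recurrence set the final size of 672. Power of about 19% for recurrence would follow only if 0.4 were carried over, which the text does not say.
- **The exact value.** A reader might infer that only 0.04 can have been used. The 42 patients per hospital is inferred from 336/8, and a continuity-corrected calculation with an ICC near 0.032 and m = 42 comes within 3% of both sizes. The firm statement is about one tenth of 0.4, with 0.04 the best fit.
- **The regional range.** The Background reports colostomy rates of 31% to 41% across Ontario regions. An ICC of 0.4 around 30% implies a between-hospital SD of √(0.4 × 0.30 × 0.70) = 0.29, and 0.04 implies 0.09. Regional averages smooth hospital differences, so the range cannot decide between these values.
- **Conduct.** If the figure is a misprint, the sizes and the 80% are right and nothing about the trial's conduct changes.

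That the full protocol is not shown is no answer: the article prints both the ICC and the size said to rest on it.

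**Conclusion.** The point holds for permanent colostomy. An ICC of 0.4 contradicts 8 hospitals and 311 patients per arm at 80% power under every standard variant tried. At 0.4 the effective size is at most 20 per arm against about 118 needed, and power is about 20%. The stated size corresponds to an ICC of about 0.03–0.043. The match of 0.04 to both 311 and 336 makes a decimal slip the most plausible explanation, but this is an inference; the article does not confirm it. The recurrence size is corroborating evidence and is not itself contradicted.

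The conclusion rests on equal cluster sizes, the usual design effect and no allowance for loss to follow-up (none is stated). Whether the 80% claim is wrong depends on the source estimate: it stands if that was 0.04 and fails for colostomy if it really was 0.4.

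**What to change.** Check the analysis of the 1997 to 1999 hospital data that produced the ICC.

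- If it gave 0.04, correct the printed value and leave both sample sizes and the 80% power as they are.
- If it really gave 0.4, state that power for colostomy is about 20% at the planned size, without changing enrolment.
- In either case, report the ICC and the patients per hospital actually used for the local recurrence calculation. The authors should take these from their records; the 0.04 and 42 back-calculated here should not be adopted unverified.

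The cost is one corrected figure or one restated power, plus a sentence on recurrence. Hospitals, patients and data collection are unaffected.
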